**Principal outcome**											
Car use reduction (kilometers and modal share)	Sensedoc and/or mobility logbook		✓^abc^		✓^abc^	✓^abc^	✓^abc^	✓^bc^	✓^bc^	✓^ab^	✓^bc^
**Secondary outcomes**											
Use of active and sustainable mobility (kilometers and modal share)	Sensedoc and/or mobility logbook		✓^c^	✓^c^	✓^c^	✓^c^	✓^c^	✓^c^	✓^c^	✓^c^	✓^c^
Minutes of moderate and vigorous physical activity	Sensedoc and/or IPAQ [60]		✓^a^		✓^a^	✓^a^	✓^a^	✓	✓	✓^a^	✓
Exposure to air pollution	MicroPem		✓				✓			✓	
Carbon footprint related to transport	Calculation based on the travelled kilometers and the mode of transport		✓^c^		✓^c^	✓^c^	✓^c^	✓^c^	✓^c^	✓^c^	✓^c^
Quality of life	Survey SF-12 [61]		✓			✓	✓		✓	✓	✓
Biometrics	Biometrics survey (size and weight)		✓^c^		✓^c^	✓^c^	✓^c^			✓^c^	
Activity programme	Mobility logbook		✓^c^	✓^c^	✓^c^	✓^c^	✓^c^	✓^c^	✓^c^	✓^c^	✓^c^
Mobility diagnosis	Survey		✓								
Accessibility by public transport and bicycle	Calculation of spatial information through a survey		✓^c^								
Cyclability	Calculation of spatial information through a survey		✓^c^								
Socio-demographic information survey	Survey		✓								
Socio-demographic follow-up survey	Survey				✓	✓	✓	✓	✓	✓	✓
Psychological constructs survey part 1			✓				✓	✓	✓	✓	✓
Stage of mobility change	Adapted survey [62]		✓				✓	✓	✓	✓	✓
Associated mobility habits	Adaptated survey [63]		✓				✓	✓	✓	✓	✓
Green identity	Survey [64]		✓				✓	✓	✓	✓	✓
Psychological constructs survey part 2			✓		✓	✓	✓	✓	✓	✓	✓
Mobility habits	Adapted survey [65]		✓		✓	✓	✓	✓	✓	✓	✓
Intention towards mobility	Adapted survey [66]		✓		✓	✓	✓	✓	✓	✓	✓
Mobility self-efficacy	Adapted survey [66]		✓		✓	✓	✓	✓	✓	✓	✓
Intention implementation towards active mobility	Adapted survey [66]		✓		✓	✓	✓	✓	✓	✓	✓
Mobility attitudes	Adapted survey [66]		✓		✓	✓	✓	✓	✓	✓	✓
Perceived risks of COVID-19	Adapted Survey [67]		✓		✓	✓	✓	✓	✓	✓	✓
Mobility subjectives norms	Adapted survey [66]		✓		✓	✓	✓	✓	✓	✓	✓
Psychological constructs survey part 3	Adapted survey		✓		✓	✓	✓	✓	✓	✓	✓
			✓								
Satisfaction with travel	Adapted survey [68]		✓								
Mobility motivation	Adapted survey [69]		✓								
Psychological constructs survey part 4			✓^b^		✓^b^	✓^b^	✓^b^	✓^b^	✓^b^	✓^b^	✓^b^
Subjective vitality	Adapted survey [70]		✓^b^		✓^b^	✓^b^	✓^b^	✓^b^	✓^b^	✓^b^	✓^b^
Tentation and conflict	Adapted survey [71]		✓^b^		✓^b^	✓^b^	✓^b^	✓^b^	✓^b^	✓^b^	✓^b^
Reach of the intervention	Ratio of contacted people, eligible and enrolled people	✓^c^									
Quality of the implementation	Checklist for every intervention meeting (answered by the programme implementer)			✓^c^	✓^c^						

*Note*. By default, the outcomes were measured by using a survey that was filled in at the beginning of the session. S = Seven-day measurement session (except from S0+ that indicated the first intervention meeting), R = Recruitment and enrolment periods. ^a^ indicates that the outcome was measured with a sensor, ^b^ indicates that the outcome was measured on a daily basis, ^c^ indicates that the outcome was calculated by a member of the research team based on other data

**Fig. 5 Fig5:**
[figure not shown]
Data collection sensors. In the left side, Sensedoc™ sensor (Accelerometer and GPS) which should be worn in a belt around the waist. In the middle, MicroPem™ (pollution sensor) which should be worn in a bag or purse with the pipe as close to the airway as possible. In the right side, the MicroPem™ and the Sensedoc™. Source: Figure created by authors

Approximately 1 month after the beginning of the study, participants have the second meeting of the intervention (1 hour) and start a new session of measurement (S1). During this session, they carry a Sensedoc™ and answer the same surveys as in S0. Approximately 3.5 months after the start of the study, the participants have the third session (S2) containing the same elements as in S0 except for the pollution sensor. Then, about 7 months after the start of the study, the intervention is finished and immediately after the end of the intervention, the participants have the fourth session (S3) during which they carry the Sensedoc™ and the MicroPem™ and answer the same surveys as in S0. Around 9 months after the start of the study, participants start the fifth session (S4), they do not carry any sensors but fill up a mobility logbook and answer the same as in S0. Twelve months after the start of the study, participants start the sixth session (S5) with the same protocol as S4. Eighteen months after starting the study, participants start the seventh session (S6) following the same protocol as S0. Finally, 24 months after starting the study, participants start the eighth session (S7) and follow the same protocol as S4 and S5 (see Fig. 4).

All the sessions are scheduled with our management tool by considering the availability of the programme implementers. This internal tool is central to implement and chart all steps of the intervention.

#### Retention of participants

To limit the attrition risk, the implementation team will send a newsletter including information about the study (e.g., recruitment ratios) and the research team (interviews, recommended scientific articles) a few times a year. Moreover, participants taking part in the study until the session 2 will be drawn to win a connected watch.

#### Power analysis and sample size

Sample size is difficult to estimate when using multilevel modelling as in the present study, given that sample size calculation is sensitive to the values of all the fixed and random parameters included in the models. As such, we estimated the sample size based on the expected effect size of the intervention at the end of the intervention only, which was an expected difference of 17% of the trips made by car at the end of the intervention [72] between the experimental and the control group. With a significance level of 0.05 and a statistical power of 80%, the a priori power analysis conducted with G*Power 3.1.9.4 [73, 74] indicated that 150 participants per arm (a total of 300 participants) are necessary for finding a difference of 17% between the experimental and the control arms at the end of the intervention. We will therefore recruit participants until exhaustion of our financial and human resources, with this ideal target of 150 participants per arm. Once recruitment is finished, we will compute the minimal statistically detectable effect that can be observed based on the final number of participants [75].

### Interventions

Eligible participants will be randomised in equal proportion to the experimental arm or to the active control group. The duration of both interventions will be the six first months of the 24-month study period (Fig. 4). The detailed content of each arm will be described in the next subsections.

#### Experimental arm

The participants attributed to the experimental arm will receive a free six-month transport pass and/or a six-month free access to a classic or electric bike (behavioural technique classified as “12.5 Adding objects” according to [27]). They will have two meetings with a programme implementer who will deliver behavioural change techniques, including a discussion about the motivation to change (behavioural techniques known as “motivational interviewing” and “5.2 salience of consequences” according to [27, 76]), personalised transport advice (behavioural technique classified as “4.1 Instructions on how to perform the behaviour” according to [27]), a mobility change goal setting and action planning (behavioural techniques classified as “1.1 Goal setting” and “1.4 Action planning” according to [27]), and obstacles’ prevention (behavioural technique classified as “1.2 Problem solving” according to [27]).

More precisely, during the first intervention appointment with the programme implementer called “S0+” (1.5 hours), the participant and the programme implementer will discuss about the motivations to change, they will work together on a personalised transport advice considering the participant’s needs, constraints and preferences, the participant will set some change goals and elaborate an action plan, and he/she will examine the possible obstacles to change and how to prevent them. During the second meeting (1 hour, see Fig. 4), the programme implementer and the participant will assess and adapt the previously established goals, they will work on an updated personalised transport advice (if the participants ask for it), and on resolving any obstacles they met since the first meeting that have not been resolved.

Following the first meeting of the intervention, participants will be prompt to fill up a “goal notebook” during the 6 months of the intervention, by setting or reviewing their goals every 2 weeks, and by taking notes of the experienced obstacles. In addition, they will receive weekly SMS during the first 3 months of the intervention, and bimonthly SMS during the last 3 months of the intervention, to a) prompt goal setting and try to keep the same contexts for the goals like the same trips or the same transport modes (behavioural techniques classified as “1.7 Review outcome” and “8.2 Habit formation” according to [27]) and b) prompt self-monitoring related to the consequences of mobility change (e.g., a more important well-being; behavioural technique classified as “2.4 Self-monitoring of outcomes” according to [27]).

#### Active control arm

The participants in the active control arm will also have two meetings with a programme implementer, of the same duration as in the experimental arm. During the first 1.5 hour meeting “S0+”, the programme implementer and the participant will discuss about air pollution (i.e., definition of air pollution sources, population most impacted, air pollution levels in Grenoble, health consequences of pollution and pollution peaks), about the association between air pollution and mobility (i.e., participants and programme implementer discuss about the exposure of car drivers and bike drivers to air pollution), and about the advantages of commuting by car (behavioural technique classified as “5.2 Salience of consequences” according to [27]). During the second 1-hour meeting, the participant and the programme implementer will discuss of the air quality of the last weeks and check if there were some pollution peaks during the last weeks (behavioural technique classified as “5.2 Salience of consequences” according to [27]).

Following the first meeting, participants will be prompt to fill up an “observation notebook” during the 6 months of intervention, by taking notes of air quality and of every announcement of pollution peak every 2 weeks. In addition, they will receive weekly SMS during the first 3 months of the intervention, and bimonthly SMS during the last 3 months of the intervention, to prompt taking notes of a) air quality and b) any pollution peak announced in the television/radio/telephone (see Table 2 for a summary of the interventions for the experimental and active control arms).

**Table 2 Tab2:** Summary of the elements of the experimental and the active control arms

Element	Experimental arm	Active control arm
**Material incentive**	6 months of free transport and/or 6 months of free access to a classic or an electric bike	
**2 appointments with a programme implementer**	First appointment: Discussion about the motivations to reduce car use, co-construction of a personalised mobility advice, mobility change goals setting, development of an action plan, prevention of obstacles to change mobility behaviour. Second appointment: Evaluation and adaptation of change goals and resolution of obstacles	First appointment: Concept of air pollution, in-depth questions on pollution (sources of air pollution, health consequences, pollution levels in Grenoble metropolitan area), discussion about the association between air pollution and car use and discussion about the benefits and advantages of the frequent use of the car Second appointment: Evaluation and discussion of the air quality and the identified pollution peaks
**Notebook to be filled up**	Goals notebook: 1. Setting new goals or adapting goals every two weeks 2. Taking notes of the experienced obstacles (if any) and looking for solutions	Observation notebook: 1. Taking note of the air pollution every two weeks 2. Taking note of the announced air pollution peaks (if any)
**2 kinds of SMS** **(1 SMS per week during the first 3 months and 1 SMS bimonthly during the last six months)**	1. Prompting the Setting and the Adaptation of goals, action planning and, habit formation 2. Self-monitoring of positive consequences of mobility change (e.g., better physical state, feeling of well-being)	1. Taking notes of the air pollution indices and comments 2. Taking notes of the announced air pollution peaks and comments

#### Adherence

To measure the adherence to each intervention arm, the programme implementer will take notes of the duration of each meeting and of every situation that could disrupt the planned content of the intervention (e.g., participants that do not receive any personalised transport advice). Moreover, one item in the deployed surveys will assess whether the participant sets goals (i.e., Intention implementation towards active mobility survey, see Table 1).

### Outcomes and data collection

#### Primary outcome and data collection methods

The main outcome of InterMob study will be the reduction of car use measured by kilometres travelled by car and the modal share of the car. This outcome will be calculated from segmented and enhanced GPS tracks obtained from a sensor containing a triaxial accelerometer and a continuous GPS tracking MAX-M8 Global Navigation Satellite System receiver from u-blox (Sensedoc™ 2.0, see Fig. 5), and by a mobility logbook (i.e., a paper notebook collecting detailed information on the activities and trips made each day, such as departure and arrival times, the address of the arrival point; the transportation mode, the number of people making the trip with the participant). More precisely, The SenseDoc™ 2.0 acquires GPS data each second et accelerometry with a frequency of 60hz.

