**Fig. 1 Fig1:**

Followed steps for the elaboration, implementation and evaluation of InterMob. Source: Figure created by authors

In conclusion, InterMob is a 24-months randomised controlled trial, parallel group, two-arm, superiority trial with 1:1 allocation ratio.

The objectives of the study are to:

Evaluate the effectiveness of the InterMob intervention in reducing car use in the short- and in the long-term (one, three, seven, twelve, and twenty-four months after the beginning of the intervention).Identify the mechanisms underlying mobility behaviours and behaviour change (e.g., psychological constructs such as intentions, self-efficacy, habits).Identify the moderators of mobility change (i.e., the conditions and contexts under which the intervention is effective such as family context, degree of cyclability, trip chaining, work situation, activities organisation in space and time).

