#### Statistical methods

##### Analysing the effects of the intervention on primary and secondary outcomes by using multilevel modelling

The analysis of the effectiveness of the intervention on the primary outcome (reduction of car use, see "Primary ouctome and data collection methods") and secondary outcomes (mobility-related variables described in the section "Secondary outcomes and data collection methods") will be examined at the very short term (3 months after the start of the intervention: S2), the short term (7 months after the start of the intervention: S3), the medium term (1 year after the start of the intervention: S5) and the long term (18 months after the start of the intervention: S6). More precisely, we will test the differences in car use reduction between the experimental arm and the active control arm, by using multilevel modelling, which is appropriate when data are nested, as it is the case here with several measurement times per participant (e.g., [78]). Moreover, multilevel modelling offers the possibility to analyse incomplete data sets, which is particularly relevant given the duration of the study, which makes likely the occurrence of missing data [79]. For this purpose, we will follow the steps recommended by [80]:Prepare the data by differentiating between- and within-individual constructs.Centre the within-individual variables by participant (i.e., “group centring”).Create a first “constraint” model (a model containing all the random and fixed variables of the final model) and a “null” model including only the “intercept” equal to 1 and only one random variable associated with the identity of the participant (i.e., 1 | Id) to check the intraclass correlation coefficients (ICC).Build the main model.Evaluate the normal distribution of residuals, Cooks distance and influential cases.

The main model will include the following fixed effects: arm, time, and arm x time interaction, with random intercepts for participants and random linear slopes for repeated measures at the participant level.

Moreover, the statistical analysis will follow intention-to-treat principles. This means that once a participant has been randomly assigned to an arm (i.e., experimental or control), his/her data will be included in the analysis [81]. More precisely, even if a participant has not adhered to the intervention or has not finished the study, his/her data will be included to all the analysis.

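### The primary claim has no single deciding test: two unranked measures are examined at four sessions, while the sample size covers one measure at one session

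*Protocol article*

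**What the plan says.** The section on the primary outcome defines it as "the reduction of car use measured by kilometres travelled by car and the modal share of the car". Table 1 lists the same two quantities on one line under the principal outcome, again without rank.

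The statistical methods say that the effect on this outcome "will be examined at the very short term (3 months after the start of the intervention: S2"), and then at S3 (7 months), S5 (1 year) and S6 (18 months). The main model has arm, time and arm-by-time as fixed effects. The section does not say which term or contrast answers the primary question.

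The sample-size section is narrower: "we estimated the sample size based on the expected effect size of the intervention at the end of the intervention only". The target is "an expected difference of 17% of the trips made by car at the end of the intervention", and the calculation uses "With a significance level of 0.05 and a statistical power of 80"%. It concludes that "150 participants per arm (a total of 300 participants) are necessary for finding a difference of 17"% between the arms. The timeline places S3 immediately after the intervention ends, at about 7 months, so the sized comparison is the one at S3.

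The objectives list a different set of times for short- and long-term effectiveness: 1, 3, 7, 12 and 24 months.

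**The concern.** Two measures at four sessions give eight arm comparisons on the primary outcome. The article sizes the trial for one of them but does not name that one, or any other, as the comparison on which the claim rests. A reader of the final report could not tell whether a difference in kilometres at 12 months with none in modal share at 7 months, or the reverse, counts as success. The stated 0.05 and 80% describe one comparison; they do not describe the primary question as the article defines it.

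**Working it through.** **Inputs.** From the article: 0.05, 80% power, a 17% difference in trips by car, 150 per arm, a "superiority trial with 1:1 allocation ratio", two measures and four sessions. Assumed, because the article does not give them: two-sided testing, the base rate of car trips, and all correlations between sessions and between measures.

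**1. The plan's own figure.** For two proportions, n per arm = [z₀.₉₇₅·√(2p̄q̄) + z₀.₈·√(p₁q₁ + p₂q₂)]² / d². With an absolute difference d = 0.17 and assumed rates of 58.5% and 41.5%:

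[1.960 × 0.7071 + 0.8416 × 0.6968]² / 0.0289 = 135 per arm.

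With continuity correction this becomes 147. Fisher's exact test has 79.8% power at 144 per arm and 82.6% at 150. So 150 is reproduced closely for one two-sided test at 0.05, with a base rate near 50%. Without continuity correction, 150 per arm gives 84% power at these rates. A relative 17% reduction would need 482 per arm (base 53%) or 333 (base 63%), so the absolute reading fits.

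**2. Eight independent tests.** 1 − 0.95⁸ = 33.7% for a difference in either direction. In favour of the experimental arm only: 1 − 0.975⁸ = 18.3%, against a nominal 2.5%.

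**3. Correlated tests.** The eight statistics come from the same people, so independence gives an upper bound. The table shows the chance of at least one |z| > 1.96 under no effect, from 1,000,000 multivariate-normal draws (2 measures × 4 sessions, exchangeable correlation).

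| Correlation between sessions / between measures | Either direction | Favouring experimental arm |
|---|---|---|
| 0 / 0 | 33.7% | 18.3% |
| 0.3 / 0.3 | 31.1% | 16.0% |
| 0.5 / 0.5 | 26.9% | 13.5% |
| 0.7 / 0.7 | 20.8% | 10.4% |
| 0.8 / 0.8 | 17.2% | 8.6% |
| 0.9 / 0.9 | 12.9% | 6.45% |

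**4. One joint test over time per measure.** The arm-by-time model allows this. It leaves two tests: 1 − 0.95² = 9.75% if independent, and 7.8% at correlation 0.8.

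**5. Keeping all eight.** Bonferroni gives 0.05/8 = 0.00625. At 58.5% against 41.5%, 80% power then needs 220 per arm, and 150 per arm has 58% power for each test. Two measures at one session, each at 0.025, need 164 per arm.

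**6. Time points side by side.** Objectives: 1, 3, 7, 12, 24 months. Statistical methods: 3, 7, 12, 18 months. Three are shared (3, 7, 12). The long-term point is 24 months in one and 18 in the other, and the 1-month point is in the objectives only. Counting the five times in the objectives with two measures, the independent bound is 1 − 0.95¹⁰ = 40.1%.

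**The case against.** A reader might infer that the plan tests each of eight comparisons at 5%, and that its chance of falsely claiming effectiveness is therefore 20–34%. The document does not support that:

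- The only 0.05 stands in the sample-size section. The statistical methods give no level per comparison.
- The model could be read through one joint test per measure, which gives 8–10%.
- The 34% needs independence, which is implausible for related measures repeated in the same people. The 20% is not a floor either, because strong correlation gives 13–17%.
- Those figures count differences in either direction. A false finding in favour of the experimental arm is roughly half as likely.

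Two further objections have weight. The article condenses a fuller plan that is not shown, and alpha allocation and testing order commonly belong there. Also, the labels very short, short, medium and long term suggest a description of the time course, not interchangeable chances of success.

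These objections limit the size of the problem but do not remove it. The point does not rest on a missing alpha split. The article itself fixes two unranked primary measures and four sessions, then sizes for one measure at one session without making that comparison the primary one. The definition of the primary outcome is protocol content. A time-course purpose would fit well with one named test and supportive estimates at the other sessions, but the article does not set it out that way.

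**Conclusion.** The point stands in conditional form. The article names no measure, session or model term as decisive, and its sizing covers only one of the eight comparisons that it lists.

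No reading of the text as it stands gives a controlled 5%. If any of the eight comparisons at two-sided 0.05 may carry the claim, the error is about 13–34% for correlations from 0.9 down to 0, and about 21–27% for 0.5–0.7. For false findings favouring the experimental arm it is about 9–18% against 2.5%, for correlations of 0.8 down to 0. With one joint test per measure it is about 8–10%. The correlations and the two-sided level per comparison are assumptions. The power figures for all eight comparisons also rest on an assumed base rate.

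Separately, the objectives and the statistical methods disagree on the time points, and that needs no assumption to see.

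**What to change.** Name one primary test: the arm difference in car modal share at S3, as a stated contrast from the multilevel model. Define modal share as share of trips, since the primary outcome section does not say whether it is a share of trips or of distance. This is the comparison for which the trial was sized, so the 150 per arm target needs no change on this account.

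Make car kilometres at S3 the first key secondary, tested at 0.05 only if the primary test succeeds. Report the other sessions with confidence intervals as supportive.

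Reconcile the time points in the objectives with those in the statistical methods first. Only then place a long-term session, if one is wanted, in the fixed sequence.

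The cost is protocol and analysis-plan wording. The price is that kilometres, if the first test fails, and results at other sessions can no longer be claimed as primary evidence. Keeping all eight comparisons with Bonferroni would instead mean about 220 per arm under the assumed rates. That looks out of reach for a trial that says "We will therefore recruit participants until exhaustion of our financial and human resources". The article says that the researchers who analyse the data are blinded to allocation, so the choice can still be made credibly if it is recorded before unblinding.
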